### Statistical methods

#### Analysis plan

Analysis will be conducted once data collection is complete. No interim analyses will be performed. Initially, the quality and completeness of the data will be assessed. If available, missing values will be entered using information from the individual’s original data file. The dataset will be examined for outliers and inconsistencies. For categorical variables, any responses outside the defined categories will be coded as missing. For continuous variables, values outside the acceptable ranges will also be coded as missing. Missing data will not be imputed.

The analyses will be carried out by the investigators and a biostatistician using the latest version of SPSS Statistics (IBM Corp.), R (R-core team) or equivalent statistical software. For the analysis of functional MRI data, additional software tools described below will be used. Data analysts will be blinded to the participants’ allocation. Significance testing will be two-tailed, and statistical uncertainties will be reported as 95 % confidence intervals. All tests will be conducted with a significance level of 0·05.

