#### Primary analysis

For the statistical analysis of functional neuroimaging data, MATLAB and Statistical Parametric Mapping (SPM12) software will be used to assess brain activity patterns and differences across groups. Connectivity analysis will be performed using the CONN Toolbox to examine the relationships between different brain regions and networks. Neuroimaging data will first undergo pre-processing to ensure the data is suitable for further statistical analysis.

The pre-processing steps that will be performed include the following:Realignment: This is the process of correcting head motion of the participants.Slice-Time Correction: This involves correcting for functional differences between slices acquired every 3 s.Coregistration: Anatomical and functional images are overlaid to determine the anatomical location of activation.Spatial Normalisation: This process accounts for individual brain shapes by normalising anatomical MRI images. The template developed by the Montreal Neurological Institute will be used.Smoothing: This is used to improve image quality and will be performed using a 3D Gaussian kernel (full width at half maximum = 8 mm).

After the pre-processing steps, the data of all participants will be registered to the common Harvard–Oxford Cortical Atlas space. Participant and group-level regression analyses will be performed in this atlas space. Functional connectivity analyses will be performed between regions of the components of the Salience Network, including the anterior insula, dorsal anterior cingulate cortex, temporoparietal junction and hypothalamus. Changes in the topology of networks formed by these four regions, in addition to their functional connectivity with each other, will be analysed using Graph Theory. The changes in the connectivity features of these regions before and after caloric/non-caloric intake will be evaluated using both nodal and global metrics. Significant results obtained will be recalculated using masks transferred back to the participant space. Beta values of the regression analysis will be controlled for type-1 errors with false discovery rate and reported accordingly.

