#### Sample size calculation

A two-tailed power calculation for 70 % power and *P* = 0·05 was performed using G * Power software, for a *t* test with linear regression (two independent groups) and an effect size of d = 0·6, based on results from similar neuroimaging studies^(42)^, determining that thirty-four participants per group (AN/healthy) would be sufficient. To account for potential dropouts or unforeseen issues, thirty-six participants will be recruited for each group to ensure robust statistical analysis.

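### Only significant results are recalculated in participant space, in the same participants, so those estimates are inflated; the text also leaves open that FDR is applied after this selection

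*Protocol article*

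**What the plan says.** The Primary analysis section of the Protocol article places the participant-level and group-level regressions in a common atlas space. It names four regions, asks for their mutual connectivity, and adds graph-theory metrics at nodal and global level without giving their number. Two consecutive sentences then read: "Significant results obtained will be recalculated using masks transferred back to the participant space" and "Beta values of the regression analysis will be controlled for type-1 errors with false discovery rate and reported accordingly".

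The only threshold given is in the Analysis plan section: "All tests will be conducted with a significance level of 0·05". That section also says "Significance testing will be two-tailed" and promises 95% confidence intervals.

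The article does not say which threshold makes a result significant for the recalculation, which tests form the FDR family, or whether FDR comes before or after the recalculation. It does not say whether the recalculated values are inferential or descriptive, and it mentions no independent sample for them.

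**The concern.** Two separate matters arise, and they differ in how firmly the text supports them.

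The first follows from the stated rule itself. Only significant results reach the participant-space step, and the same participants are used to select and to re-measure. An estimate kept because it crossed a threshold is on average too large. The second figure shares its sampling error with the first, so close agreement between them says little about whether the effect is real.

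The second depends on how the paragraph is read. If significant means uncorrected p < 0.05 under the general rule, and FDR is then run only on the survivors, the correction acts on a set already screened at the level it is meant to enforce.

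This is the primary outcome. At stake are the size of the reported connectivity effects and, on the second reading, the false-positive rate behind the main conclusion.

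**Working it through.** **Inputs from the article.** Two-sided α = 0.05 (Analysis plan). Sample size calculation: "A two-tailed power calculation for 70 % power", "an effect size of d = 0·6", "thirty-four participants per group (AN/healthy) would be sufficient", and "thirty-six participants will be recruited for each group". Four named regions give 4 × 3 / 2 = 6 pairwise connections if each region is one node.

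**Assumptions, not in the article.** A family of 6 to 30 tests, independent of each other; an FDR level of q = 0.05 by the Benjamini-Hochberg (BH) procedure; a smaller true effect of d = 0.3; correlations of 0.9 and 0.7 between atlas-space and participant-space statistics.

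**The plan's own figure.** n per group = 2 × ((1.960 + 0.524) / 0.6)² = 34.29, which rounds up to 35. The noncentral t calculation gives 36, and power at 34 per group is 0.684. The stated 34 at 70% power is reproduced within rounding. It matters here only as the source of d and n.

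**Step 1: inflation from selection.** With n per group, the standard error of d is about √(2/n), so for n = 36 it is 0.2357. Let m = d / SE, c = 1.96, and P = Φ(m − c) + Φ(−m − c), the chance of selection. The mean estimate among selected results is SE × {m + [φ(c − m) − φ(c + m)] / P}.

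- d = 0.6: m = 2.546, P = 0.721, φ(c − m) = 0.336 and φ(c + m) is negligible. Mean = 0.2357 × (2.546 + 0.336 / 0.721) = 0.71, or 1.18-fold.
- d = 0.3: m = 1.273, P = 0.247, and the difference of the two densities is 0.315 − 0.002 = 0.313. Mean = 0.2357 × (1.273 + 0.313 / 0.247) = 0.60, or 2.0-fold.

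Simulation gives the same means (0.709 and 0.599). If the recalculated statistic is not identical to the original, some inflation remains at d = 0.6: the mean is 0.70 at correlation 0.9 and 0.68 at correlation 0.7. Selecting by full-family FDR instead of p < 0.05 gives means of 0.78 to 0.84 for a true 0.6. Putting FDR first therefore does not cure the inflation.

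**Step 2: FDR after selection, p-values unchanged.** BH on k survivors rejects all of them if the largest p-value is at or below q × k / k = q. Every survivor has p < 0.05 = q, so all pass. The chance of at least one false finding when nothing is true is then the uncorrected one, 1 − 0.95^m for m tests.

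**Step 3: FDR after selection, p-values changed.** Recalculation would alter the p-values, so BH on the subset can remove some results. This was simulated with every null true.

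| Null tests | 1 − 0.95^m | After selection, p unchanged (simulated) | After selection, correlation 0.9 | Full-family BH |
|---|---|---|---|---|
| 6 | 26.5% | 26% | 16% | about 5% |
| 20 | 64.2% | 64% | 40% | about 5% |
| 30 | 78.5% | 79% | 51% | about 5% |

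At 20 null tests, BH on the subset removes about 48% of the selected results at correlation 0.9. At correlation 0.7 it removes about 73%, and the chance of any false finding is 23%.

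**The case against.** The best reply is that sentence order is not order of operations. The FDR sentence refers to the betas of the regression analysis, and the regressions the section names are the atlas-space ones. On that reading FDR covers the whole family, significant already means FDR-significant, and error is controlled. The paragraph is not chronological elsewhere either: it mentions group-level regression before the connectivity and graph measures that must exist to be regressed. This stands. A reader might infer that the plan's FDR step removes nothing, but the documents do not support that as a statement of the plan. It needs uncorrected selection, FDR confined to the survivors, and unchanged p-values, and the article states none of the three.

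A second reply is that the participant-space step may be only a registration check, since the article never calls it confirmation. It also does not say that betas are reported only for significant results, and the regions are named in advance, so this is not a free voxel search. All of that is fair, although the Discussion allows region selection to be updated. It limits how the values would be misread. It does not remove the bias in participant-space estimates that exist only for significant results.

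A third reply is that family, level and order may be left to a fuller plan. As missing detail alone, that would be no finding. The selective recalculation, however, is a rule the article states, and it can be changed.

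Finally, error rates that assume one fixed number of metrics, or inflation figures for a meal-by-AN interaction, are not properties of this plan. The article gives no metric count, and its list of independent variables contains no such interaction. Neither is relied on here.

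**Conclusion.** The point holds in two parts of different strength.

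Without condition on where FDR sits: participant-space betas are computed only for significant results and in the same participants, so they are biased away from zero and are not independent evidence. With selection at p < 0.05 the size is about 1.2-fold at d = 0.6 with 36 v 36, and about 2-fold at an assumed d = 0.3.

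Conditionally: the text permits a reading in which FDR follows selection at p < 0.05, and on that reading it gives little or no protection. The chance of any false finding is about 26% to 79% with unchanged p-values and about 16% to 51% at correlation 0.9, against about 5% with full-family FDR. These ranges rest on the assumed 6 to 30 independent null tests and on BH at q = 0.05. They illustrate what the ambiguity could cost and do not estimate the trial's actual error rate. If FDR is applied to the full atlas-space family first, this second part disappears and only the inflation remains.

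**What to change.** 1. State that FDR is applied once, at a named level, to the full set of atlas-space tests before any selection. The set should cover all connections, all nodal and global metrics, and all terms of interest.
2. Run the participant-space recalculation for all four regions and all pairs whether or not they were significant, and label it a descriptive sensitivity analysis.
3. Report betas with 95% confidence intervals for every connection.

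The cost is a change of wording and slightly more analysis work. No new data or participants are needed, and the article says analysis begins only once data collection is complete. The downside is that fewer results may be declared significant.

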## Abstract

Anorexia nervosa (AN) is an eating disorder that is mediated by psychological and metabolic factors, yet it is unclear how these factors interact. The NAMA trial objective is to clarify the metabo–psychiatric interaction and identify how it affects AN patients’ behaviour. This randomised trial will recruit thirty-six treatment-naïve female AN patients, 13–18 years of age, and thirty-six matched healthy controls. Participants will undergo psychiatric assessments followed by 12-h overnight fasting. The next morning, baseline assessments of outcomes will be performed. Patients will be randomly allocated 1:1 to receive a mixture with calories or receive a mixture without calories. Healthy controls will also be allocated to receive mixtures with/without calories. Mixtures will be standardised for taste and appearance, and allocation will be masked. The primary outcome measure is resting-state functional MRI 60 min post-consumption of the mixture. Secondary outcomes include (1) blood samples to study markers reflecting metabolic states, hunger/satiety and stress responses, (2) psychometric evaluations of subjective experiences and (3) assessment, in a second meal 3 h later, of the effects of previous calorie intake on subsequent food consumption. This article describes the study protocol, including the analysis plan, for a randomised controlled trial to comprehensively evaluate the effects of calorie intake in AN. The trial will distinguish psychological and metabolic neuronal networks associated with food intake and uncover how their integration affects food intake and other hallmark symptoms in AN. The aim is to accelerate treatment development by identifying brain mechanisms that drive AN.

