While these observations indicate that neuronal networks in the brain integrate metabolic and psychological aspects of eating differently in AN, it is unclear how this perturbed metabo–psychological integration contributes to AN development and maintenance^(52)^. No previous report has, to our knowledge, revealed in what way the connection between psychology and metabolism mediates core symptoms of AN; that is, no one has distinguished either what neuronal networks respond to the psychological *contra* metabolic aspects of eating a meal or how those networks integrate their information to affect patients’ food intake, distorted body image and fear of weight gain. The identification of the mechanisms that drive AN is also hampered by the current tendency of published studies to focus on adults rather than adolescents although adolescence is the time when most patients develop AN. The ISRCTN and Clinicaltrials.gov registers (as of October 2025) record neither any recent nor ongoing trials anywhere in the world aimed to answer these questions. No current clinical trials of AN comprehensively speak to metabo–psychological mechanisms of change.

The primary objective of the Networks Integrating Anxiety and Metabolism in Anorexia Nervosa (NAMA) trial is to distinguish between the neural response to eating caloric and non-caloric meals and how this differs between newly diagnosed adolescents with AN and matched healthy controls. Secondary objectives examine the effects of caloric and non-caloric food intake on endocrine, circulatory, psychological and behavioural responses in patients with AN and healthy controls. By integrating behavioural, psychological and physiological aspects of food intake with brain network analyses, the NAMA trial will investigate what drives AN. We hypothesise that calorie-dependent changes in network activity will differ between AN patients and healthy controls and that calorie intake will predict aggravated AN-related symptoms in patients: lower food intake, worse fear of gaining weight and increased feeling of being overweight.

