The independent variables of the regression analyses will include (1) type of meal (caloric or non-caloric), (2) AN status (AN or healthy control), (3) AN subtype (restrictive or bulimic type), (4) BMI and (5) duration of AN illness. A random effect for each participant and for each matched set of patient and healthy control will be used to account for within-subject correlations from repeated measurements and dependencies within each matched pair.

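### The primary regression names no meal-by-AN term and no single dependent variable, so no listed coefficient tests the stated primary hypothesis

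*Protocol article*

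**What the plan says.** The objectives paragraph at the end of the introduction sets the primary objective as follows: "distinguish between the neural response to eating caloric and non-caloric meals and how this differs between newly diagnosed adolescents with AN and matched healthy controls", and continues: "We hypothesise that calorie-dependent changes in network activity will differ between AN patients and healthy controls".

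Primary analysis, under Statistical methods, gives the regressors: "The independent variables of the regression analyses will include (1) type of meal (caloric or non-caloric), (2) AN status (AN or healthy control"; the list ends with "3) AN subtype (restrictive or bulimic type), (4) BMI and (5) duration of AN illness". On correlation it says: "A random effect for each participant and for each matched set of patient and healthy control will be used to account for within-subject correlations". No time term, T0 covariate or product term is named.

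The outcome is described in more than one way. The abstract has "The primary outcome measure is resting-state functional MRI 60 min post-consumption of the mixture". Primary analysis has "The changes in the connectivity features of these regions before and after caloric/non-caloric intake will be evaluated". The MRI section schedules scans at both T0 and T2.

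Secondary analyses reuses similar regression models and adds time and an allocation-by-time interaction. No interaction with AN status is named there. The sample size section powers a two-group comparison of AN with healthy participants at d = 0.6.

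**The concern.** The hypothesis is about a difference of differences: caloric minus non-caloric in AN, compared with the same contrast in controls. A regression with meal and AN status as separate variables gives both groups the same calorie effect. It can say whether calories matter on average and whether AN differs from controls on average. It does not estimate whether calories matter differently in AN, which is the question the trial was set up to answer.

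The dependent variable matters too, because the meaning of the meal coefficient depends on it. A participant random effect for repeated measurements suggests that T0 and T2 scans are separate rows. Meal type coded by allocation would then cover T0 rows, recorded before anyone has eaten.

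If the contrast and the outcome are chosen after the data are seen, the central test of the trial becomes a post hoc choice.

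**Working it through.** **Inputs from the protocol.** 36 AN patients and 36 controls; patients allocated 1:1, each control given the matched patient's meal, so about 18 per meal-by-AN cell and 36 per meal; scans at T0 and T2; two-sided 0.05; 70% power; d = 0.6 for AN versus healthy.

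**Assumptions, not in the protocol.** Unit SD at each scan; T0–T2 correlation ρ of 0.3, 0.5 or 0.7; d = 0.6 carried over to the calorie effect or to the interaction; no within-pair correlation in the power formulas.

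**The plan's own figure.** For two groups of n, SE = √(2/n). At n = 34, SE = 0.2425 and 0.6/0.2425 = 2.47. Power is 68.4% by the noncentral t and 69.6% by the normal approximation. The sample size for 70% is 36 (t) or 35 (normal), against the stated 34. The figure is reproduced to within two participants per group, but for AN versus healthy, not for the interaction.

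**What the listed coefficients estimate.** Let the calorie effect at T2 be a in AN and c in controls.

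- Hypothesised contrast: a − c.
- Meal coefficient, change-score or T2 outcome, balanced cells: (a + c)/2.
- Meal coefficient, T0 and T2 as separate rows with no time term: it averages zero at T0 with (a + c)/2 at T2, giving (a + c)/4.

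| a, c | a − c | Meal coefficient, change or T2 | Meal coefficient, both scans as rows |
|---|---|---|---|
| 0.6, 0.6 | 0 | 0.60 | 0.30 |
| 0.6, 0 | 0.6 | 0.30 | 0.15 |
| 0.6, −0.6 | 1.2 | 0 | 0 |

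A simulation (1,000 runs, 72 participants in matched pairs, ρ = 0.5) agrees:

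- Equal effects: 0.59 on change scores (68% power) and 0.31 with both scans as rows (34% power).
- AN only: 0.30 on change scores and 0.15 with both scans as rows. A meal-by-AN term on change recovers 0.60, with 23% power.
- Opposite effects: about 0.00 either way, rejected in 4% to 6% of runs. A meal-by-AN term on change recovers 1.21, with 72% power.

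The AN coefficient is no substitute. With opposite effects it averages 0.59 on change scores, but it would also move if AN patients changed differently from controls after either meal, calories or not.

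**Size of the dilution, if it applies.** With both scans as rows, the meal coefficient has SE = √((1+ρ)/2) × √(2/36). For 0.30 SD this is 0.190, 0.204 and 0.217, giving power of about 34%, 31% and 28% at ρ = 0.3, 0.5 and 0.7.

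**Power for the contrast that tests the hypothesis.** With 18 per cell:

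- T2 adjusted for T0: SE = √(1−ρ²) × √(4/18) = 0.450, 0.408, 0.337.
- Change score: SE = √(2(1−ρ)) × √(4/18) = 0.558, 0.471, 0.365.

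| ρ | Power at 0.6 SD, adjusted for T0 | Power at 0.6 SD, change score |
|---|---|---|
| 0.3 | 26% | 19% |
| 0.5 | 30% | 24% |
| 0.7 | 42% | 37% |

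On change scores at ρ = 0.5, an interaction of 1.2 SD has 71% power; 70% power for 0.6 SD would need about 70 per cell, or 4 × 70 = 280 participants.

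**The case against.** The regressor list says what the variables will include. It does not say that the model is additive, and the article may condense a fuller plan. The discussion also states that the analysis plan is deliberately loose. That stands in part: a reader might infer that the hypothesis cannot be tested at all, and the text does not support so much. It supports that the term which would test it is not named. The omission is still notable, because the section goes down to AN subtype and illness duration, and the next section does name an interaction when one is intended. The reasons given for looseness (new algorithms, new studies, choice of regions) do not bear on this contrast.

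A reader might also infer that the calorie effect is certainly halved. It is not certain. The before-after wording allows a change-score outcome, and the abstract a T2 outcome; neither dilutes a common meal effect. The abstract's 60-minute scan and the before-after comparison can also be reconciled as T2 judged against T0, so the outcome is underspecified, not plainly contradictory.

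The secondary models should not be read as leaving out AN status. They follow the primary model, which lists it; only an AN interaction is unstated. Finally, exact cancellation needs equal and opposite effects, which is an extreme case.

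**Conclusion.** The point holds in this form: the primary hypothesis is a meal-by-AN contrast, and no coefficient listed for the primary regression estimates it, whether the outcome is the T2 scan, the change, or both scans. That conclusion follows from the text and needs no numerical assumption.

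The dilution from 0.60 to 0.30 SD is conditional on both scans entering as rows with meal coded by allocation and no meal-by-time term.

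Naming the right contrast should not be taken to bring adequate power. Adjusting for T0 gives 74% to 95% for a meal main effect of 0.6 SD with 36 per meal, but the interaction at the same size has only 26% to 42%. These figures rest on the assumed correlations and on applying d = 0.6 to the interaction. Positive correlation within matched pairs would raise the interaction power somewhat.

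**What to change.** In Primary analysis:

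1. State one dependent variable, for example T2 connectivity adjusted for T0, and use it throughout, the abstract's outcome definition included. Modelling both scans with meal × AN × time is an alternative that targets the same contrast.
2. Write the model out: T2 = T0 + meal + AN status + meal × AN status, with a random effect for matched pair, plus whichever listed covariates are kept.
3. Name the meal × AN coefficient as the primary test, and report the meal effect within AN and within controls with confidence intervals.

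In Secondary analyses, add the interaction with AN status to the allocation-by-time term.

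In the sample size section, restate power for the meal × AN contrast, with the assumed correlation and effect size shown.

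The T0 scans are already scheduled, so no new data are needed. The change can be made through the protocol's own amendment route before the blinded final analysis. The real cost is disclosure: 72 participants were justified for an AN-versus-healthy comparison, and on change scores they give about 70% power only for an interaction near 1.2 SD at a correlation of 0.5.

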Patients with anorexia nervosa (AN) fear gaining weight and have a distorted body image and low body weight resulting from insufficient food intake^(1)^. AN has a devastating effect on the lives of affected individuals and a markedly high mortality^(2,3)^. Onset peaks in adolescence^(4–6)^. Adolescents, at least in Western countries, often internalise a thin-body ideal^(7–9)^. Large case–control studies have associated AN with environments emphasising dieting as well as other social and personal contexts suggested to make young individuals psychologically vulnerable to AN^(9–14)^. However, many of these contextual factors are non-specific and common to other psychiatric disorders^(13)^. Additionally, most young individuals exposed to thin-body ideals do not develop AN^(15)^. Several prospective studies have failed to identify thin-body ideal internalisation and other psychological factors related to pursuing thinness as risk factors for AN^(15–18)^. Rather, it has been shown that negative affect or neuroticism and perfectionism predict AN^(12,17,19,20)^. Psychotherapy together with nutritional rehabilitation can treat AN, yet patients frequently relapse, and remission typically takes years to achieve if achieved at all^(3,21,22)^. Hence, it is unclear how psychological factors specifically affect the development and maintenance of AN^(15,23,24)^.

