### Eligibility

Female individuals of 13–18 years of age who are currently patients at the eating disorder clinic and newly diagnosed with AN according to the Diagnostic and Statistical Manual of Mental Disorders, 5th edition^(58)^, and treatment naïve will be eligible. Healthy control participants will be matched on age, sex and education level with the AN participants. The clinical diagnosis/diagnoses for participants will be validated/ruled out by the Schedule for Affective Disorders and Schizophrenia for School-Age Children – Present and Lifetime version^(59)^. The presence of other exclusion criteria will also be further explored at the clinical visit.The exclusion criteria are as follows:Having one or several chronic medical conditions that may interfere with or hinder participation or affect study outcomes.Use of medications that affect hormone levels or eating behaviours.Having one or several severe psychiatric disorders other than AN (e.g. schizophrenia, major depressive disorder, bipolar disorder).Current drug abuse, pregnancy or potential pregnancy (for AN patients, these conditions are excluded as a part of routine care. For healthy controls, no drug testing will be performed.).High risk of refeeding syndrome or severe complications related to eating disorders.Inability to comply with the nutritional programme of the study.Allergies to foods included in the provided meal content.Cognitive impairments preventing comprehension of the study or the informed consent process.Contraindications for MRI (e.g. pacemaker, prosthesis, claustrophobia)Fasting blood sugar above 6·0 mmol/l on the morning of the study, as this indicates either non-compliance with overnight fasting or pre-diabetes/diabetes.

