#### Additional exclusion criterion for healthy controls

(1) Having one or several eating disorders, current or past.

Unexpected findings of biochemical anomalies at baseline (please see ‘Assessments’) will not be considered exclusion criteria, and medical conditions will be referred for appropriate treatment.

Participant inclusion in the study will be determined by a study clinician based on the outlined eligibility criteria. In cases of uncertainty, the principal investigator will make the final decision. Importantly, to maintain impartiality and avoid selective recruitment bias, enrolling clinicians will be masked to future treatment allocations, as randomisation will occur at a later point in time. Participants will receive both oral and written information about the study and will provide written informed consent before inclusion. For participants below 18 years of age, written informed consent will also be obtained from parents or legal guardians. Participation in the study is voluntary, and participants may withdraw at any time without any negative consequences or affected subsequent care. Participants may also choose to withdraw any personal data already collected.

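### AN subtype and illness duration are entered in a model pooled with controls, who can have neither; BMI is a separate, lesser collinearity problem

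*Protocol article*

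**What the plan says.** Under Primary analysis, the Protocol article lists five independent variables for one set of regressions: type of meal, then AN status, "2) AN status (AN or healthy control"), and then "3) AN subtype (restrictive or bulimic type), (4) BMI and (5) duration of AN illness". Subtype has two levels, and both describe patients. The same paragraph adds a random effect that "for each matched set of patient and healthy control will be used", so patients and controls are in one model.

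Four other statements bear on this:

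- The additional exclusion criterion for controls is "Having one or several eating disorders, current or past".
- The Analysis plan section states: "Missing data will not be imputed".
- Under Eligibility, "Healthy control participants will be matched on age, sex and education level with the AN participants". BMI is not a matching factor.
- The opening paragraph of the introduction says that patients with AN "have a distorted body image and low body weight resulting from insufficient food intake".

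The article states no value of subtype or duration for controls, no nesting of these terms within AN, and no patients-only model. Secondary analyses uses similar regression models, and Dose–response analyses reuses the models already specified.

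**The concern.** Two of the five covariates have no value in half of the sample. The analyst must therefore choose a coding, and the choice decides whether the AN-v-control contrast can be fitted and what its coefficient means. That contrast is the one on which the sample size rests, at 70% power and with no allowance for covariates that inflate its variance. The patient-control difference is also part of the primary objective. Because the secondary and dose–response models take over the same covariates, the fault extends beyond the primary outcome.

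BMI raises a different question. It is defined for everyone, but it is tied to group membership by the nature of the disorder and is not matched. Adjusting for it leaves less independent information about AN status.

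**Working it through.** **The plan's own figure.** Inputs from Sample size calculation: d = 0.6, two-sided 0.05, 70% power. The normal approximation gives 2 × ((1.960 + 0.524)/0.6)² = 34.29 per group; the noncentral t gives 35.27. The stated 34 is reproduced to within two per group. At the planned 36 per group the t-based power is 0.709, or 71%. This is the baseline below.

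**Subtype and duration: three codings.** The design has 36 patients and 36 controls, 18 per meal in each group.

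1. *Missing in controls, no imputation.* A complete-case fit keeps 36 rows, all patients. With intercept, meal, AN, subtype and duration there are 5 columns of rank 4, because AN is constant. No AN-v-control comparison remains.
2. *A third subtype level for controls.* Then AN = restrictive + bulimic. With intercept, meal, AN, restrictive and bulimic there are 5 columns of rank 4; adding duration gives 6 columns of rank 5. AN status is redundant. The contrast of the average of the two subtype means with the control mean is still estimable.
3. *Zero in controls.* With intercept, meal, AN, bulimic indicator and duration there are 5 columns of rank 5, so the model can be fitted. The AN coefficient is then the difference between controls and a reference-subtype patient at zero duration. If duration (mean m, SD s in patients) and the bulimic share p are unrelated, the variance of that coefficient is multiplied by about 1 + (m²/s²)/2 + [p/(1−p)]/2. The article gives no figures, so these are assumptions: p = 0.3 and a gamma duration with shape 2 (m²/s² = 2) give 1 + 1 + 0.21 = 2.21. One simulated sample of 36 from that distribution gave 3.20. Across assumed duration distributions the simulated factor was about 1.9 to 3.6.

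*Nested alternative.* With subtype and duration centred within patients and set to 0 in controls, the rank is 5 of 5, all 72 participants stay in, and the variance factor for AN is 1.0.

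**BMI.** For two equal groups whose means differ by g within-group SDs, R² between BMI and AN status is g²/(g² + 4), and VIF = 1/(1 − R²) = 1 + g²/4. The article gives no BMI means or SDs, so g is an assumption. Power uses SE = √(2/36 × VIF), d = 0.6 and 68 degrees of freedom, and takes BMI to explain no residual variance.

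| Assumed gap g | VIF | SE factor | Power, AN main effect |
|---|---|---|---|
| 0 | 1.00 | 1.00 | 71% |
| 1 | 1.25 | 1.12 | 61% |
| 2 | 2.00 | 1.41 | 43% |
| 3 | 3.25 | 1.80 | 29% |
| 4 | 5.00 | 2.24 | 20% |

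**Meal-by-AN interaction, if one is fitted.** In simulation at g = 3, its variance is multiplied by about 1.01 with BMI in the model, and by about 1.05 with BMI and zero-coded subtype and duration. Meal is balanced within each group, so these covariates carry little information about the interaction.

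**The case against.** The best defence is that this is an unstated coding convention, of a kind often left to a full analysis plan, and that one sentence repairs it: centring within patients keeps everyone in and costs no precision. The no-imputation statement also stands among data-quality rules. It does not say that a participant with a covariate that cannot apply is to be deleted, so the complete-case outcome is a literal reading and not a declared intention.

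Much of this stands. A reader might infer that controls must drop out or that the AN effect cannot be estimated. The documents do not support that: zero coding is estimable, centred coding is fully efficient, and the AN-v-control contrast survives the three-level coding. A reader might also infer that adjusting for BMI removes the contrast. It does not; it widens the standard error of the AN main effect. The primary objective concerns how the response to calories differs between the groups, and that interaction is almost untouched. The gap could also be modest: patients at high refeeding risk are excluded, and the Discussion expects few advanced cases. Whether to adjust for BMI is partly a choice of question, since the introduction argues that altered brain responses in AN are not merely due to weight loss.

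What does not stand is that nothing is wrong in the text. The article fixes the covariate list for a pooled model, and two of its entries have no value in controls. The codings an analyst would try first lose the controls, make a term redundant, or change the meaning of the AN coefficient.

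**Conclusion.** The point holds for subtype and duration as a fault in the stated model. Its effect depends on the coding: loss of all 36 controls, a redundant AN term, or an AN coefficient for a patient with zero illness duration with roughly 1.9 to 3.6 times the variance. The last range rests on assumed subtype shares and duration distributions.

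For BMI the point is narrower. Collinearity with AN status is built in, but its size is unknown. The fall in power from 71% to between 61% and 20% applies only to the AN main effect, for assumed gaps of 1 to 4 SDs and no residual variance explained by BMI. It is not a statement about the meal-by-AN contrast.

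**What to change.** In Primary analysis, and in the models of Secondary analyses and Dose–response analyses that reuse it:

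- Take AN subtype and duration of illness out of the pooled model and examine them in a patients-only model (36 patients) labelled exploratory. Alternatively, keep them nested in AN, centred within patients and set to 0 in controls, and say so.
- Make the pooled model without BMI the main AN-v-control estimate, and report the BMI-adjusted model as a sensitivity analysis.

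The cost is analysis-plan wording, best settled before unblinding; recruitment and procedures do not change. The downside is that the main AN-v-control estimate is not adjusted for weight. The plan should state this and point to the sensitivity analysis.
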